## Informed consent

This study was reviewed and approved by our hospital’s Institutional Review Board. The informed consent process will be conducted as the initial task during the baseline visit. Participants will be requested to offer a summary of their understanding of the study and study procedures prior to giving consent to participate in the study. Participants will also be given an opportunity to ask any questions, with their signature on the consent form solicited only after all questions have been answered to their satisfaction. Participants will receive the original signed consent form, and a copy will be stored by the project.

## Data collection

### Demographic and clinical data

Participants’ date of birth, sex, race, and ethnicity will be collected as part of demographic data. Objective health data that will be collected are weight, height, hbA1c, blood pressure, prediabetes/diabetes diagnosis and classification, hypertension diagnosis and classification, diabetes and blood pressure medications, and comorbid chronic conditions. These data will be collected in-person at the baseline visit and at 16 weeks from baseline and via chart review of routine care at six and 12 months from enrollment in the study.

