**Methods::**

This parallel-arm quasi-randomized control trial will be conducted between January 2022 and December 2023. Seventy adult patients recruited from a single academic medical center will be randomly assigned to receive either: i) daily ready-made frozen healthy meals or ii) a weekly produce box and recipes for 15 weeks. Participants will, additionally, take part in one individual nutrition therapy session and watch videos on healthy eating, weight loss, type 2 diabetes, and hypertension. Data on weight, height, glycated hemoglobin, blood pressure, and diabetes and blood pressure medications will be collected in-person at the baseline visit and at 16 weeks from baseline and via medical chart review at six months and 12 months from enrollment. The primary outcome of the study is weight loss at 16 weeks from baseline. Pre- and post-intervention survey data will be analyzed for changes in food insecurity, diet quality, depression, as well as self-efficacy for health eating, healthy weight, and chronic disease management. Through retrospective chart review, patients who received standard of care will be matched to intervention group participants as controls based on body mass index, type 2 diabetes, and/or hypertension.

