Study activity	Baseline visit (W0)	Week 2 (W0–W2)	Week 3 – 15 (W3–W15)	Week 16 visit (W16 ± 7 days)	6 months	12 months
Informed consent process	x					
Anthropometric data (weight, height, and blood pressure)	x			x	x	x
HbA1c	x			x	x	x
Completion of study questionnaires	x			x		
Individual nutrition counseling session		x				
Nutrition education videos			x			

**Table 2. tbl2:** Expected viewership of nutrition education videos

	Video title			
	Introduction to nutrition	Nutrition and weight loss	Nutrition and diabetes	Nutrition and hypertension
All participants	x	x		
Participants with pre-/type 2 diabetes			x	
Participants with hypertension				x
Participants with pre-/type 2 diabetes AND hypertension			x	

The control group will comprise 70 participants matched to intervention group participants based on BMI, diagnosis of pre-type 2 diabetes/type 2 diabetes, and/or hypertension. Control group participants will be identified from the electronic medical record, Epic^®^, after enrollment of all intervention arm participants has been completed. A flow chart of participant recruitment and completion of study activities is shown in Figure 1. Our study protocol adheres to the SPIRIT guidelines for clinical trial protocols (Chan *et al.*, 2013) and is registered on ClinicalTrials.gov with identifier NCT05174078.

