### Data analysis

The independent variables in this study are study arm (healthy meals, produce box, and matched controls [standard of care]), nutrition counseling and education, and time (pre-intervention, 16 weeks, six months and 12 months). The primary dependent variable (outcome) is absolute weight change at 16 weeks between groups. The secondary dependent variables (outcomes) are as follows: i) absolute weight change at six months and 12 months from baseline; ii) change in hbA1c, dosage, and number of diabetes medications; iii) change in dosage and number of blood pressure medications, and; iv) change in numeric rating from baseline to 16 weeks for food insecurity, diet quality, depression as well as self-efficacy for health eating, healthy weight, and chronic disease management. A final outcome of interest is satisfaction rating for the interventions provided in the study, measured using a non-validated questionnaire developed for this study.

Descriptive statistics will be calculated for demographic data and for each dependent variable by group, nutrition counseling and education, and time. Separate repeated-measures ANOVAs will be conducted for each dependent variable with the between subjects factor group (healthy meals, produce box, and matched controls) and the within subjects factor time (pre-intervention and 16 weeks). *Post hoc* testing will be conducted as appropriate. Effect sizes will be calculated between pre-intervention and 16 weeks to capture the changes from pre- to post-intervention. Missing data will be analyzed using an intention-to-treat strategy. Statistical analysis will be performed by a biostatistician using SAS statistical software. The biostatistician will be blinded to the intervention for each group to eliminate potential bias during data analysis.

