One limitation of this study is the relatively small sample size of 70 participants who will receive interventions. Consequently, participant attrition from the study will threaten the study power. A second limitation of the study is the lack of a parallel control group. Study controls will consist of 70 matched participants identified via the electronic health record from the same patient population as the intervention arm participants. Due to funding and ethical reasons, this study is unable to utilize a true control group for comparison with the intervention groups. Our study population faces many social challenges, including food insecurity; thus, it is important to ensure that would-be controls receive compensation comparable to the healthy food items received by intervention arm participants. The small amount of the study grant limits the ability to compensate or offer equivalent healthy food items to controls after the intervention period. A third limitation of this study is the relatively short timeline (16 weeks) in which the primary outcome will be assessed. Because this study will offer interventions for only 15 weeks, and to guard against the high attrition common in studies with a lengthy period of follow-up, assessing the primary outcome soon after completion of the interventions is deemed appropriate. With the expected weight loss of one to two pounds a week over the 15-week intervention period, the timeline for the primary outcome is still clinically meaningful. Additionally, biomarkers of interest will be collected via review of the electronic medical record at six months and 12 months from baseline. While these data will allow for the assessment of study outcomes longitudinally, a significant amount of missing data will hinder such a pursuit. A final limitation of the study is the lack of blinding to treatment arm assignment among assessors collecting self-reported data. To mitigate this limitation, during the baseline visit, self-reported data will be collected prior to random allocation to intervention arms. In addition, the biostatistician analyzing the data will be blinded to the treatment arms. Despite the aforementioned limitations, we anticipate that the results of this study will add to the growing body of scholarship on the impact of direct healthy food interventions on chronic diseases.

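### A food-arm participant who misses the week-16 visit has no primary weight, because the plan uses the medical record only at six and 12 months

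*Protocol article*

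**What the plan says.** The Data analysis section defines the endpoint: "The primary dependent variable (outcome) is absolute weight change at 16 weeks between groups".

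Three places give the source of the food-arm data, and they agree.
- Demographic and clinical data: "These data will be collected in-person at the baseline visit and at 16 weeks from baseline and via chart review of routine care". The sentence then limits the chart part to six and 12 months from enrollment.
- Abstract, Methods: "collected in-person at the baseline visit and at 16 weeks from baseline and via medical chart review at six months and 12 months from enrollment".
- Table 1 (Study design) schedules the in-person measurement as "Week 16 visit (W16 ± 7 days" and lists no alternative source for it.

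The Strengths and limitations section confirms that the food-arm participants' own records will be opened: "biomarkers of interest will be collected via review of the electronic medical record at six months and 12 months from baseline".

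Controls have no study visit. Under Study design, "Control group participants will be identified from the electronic medical record", and the abstract describes the process as retrospective chart review.

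On missing data, the Data analysis section promises an intention-to-treat strategy. Its repeated-measures ANOVA has two time levels, pre-intervention and 16 weeks. The limitations section treats drop-out as a question of power: "participant attrition from the study will threaten the study power".

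**The concern.** As written, the week-16 weight in the food arms has one source, the study visit, and a missed visit loses the primary value. The later chart weights cannot stand in for it, because the ANOVA uses only baseline and week 16. Yet participants are current patients of the practice, and their records will be reviewed anyway. A routine-care weight close to week 16 may be on file and never extracted.

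This is a matter of collection, not of the statistical model. However an analysis plan handles missing data, it cannot use a weight that nobody took from the record. An intention-to-treat analysis is also most convincing when outcomes are available for everyone randomized.

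What is at stake is the comparison with controls. If people who miss the visit tend to have lost less weight, the mean loss among attenders is too large. Control weights would come from the chart and would not depend on attending a study visit.

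**Working it through.** **Inputs from the documents**
- Planned means: controls 92 kg, meals 78.4 kg, produce 85.2 kg; SD 16 kg; power 0.80; alpha 0.05 (Sample size determination). Planned losses are therefore 92 − 78.4 = 13.6 kg and 92 − 85.2 = 6.8 kg.
- 28 per group, raised to 35 for a stated 10% attrition; 70 food-arm participants and 70 controls.

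**Assumptions, not in the documents**
- Share d of food-arm participants without a week-16 weight: 10% or 20%.
- Deficit D, the amount by which non-attenders lost less than attenders: 5 kg, with a range below.
- Share r of non-attenders with a usable chart weight: one half, with a range below. Retrieved cases are taken as typical of non-attenders.

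**The plan's own figures.** One-way ANOVA power from the noncentral F distribution is 0.805 with 28 per group and 0.789 with 27, so 28 reproduces. The 35 does not follow from 10%: 28/0.9 = 31.1, rounded up to 32. It matches 28/0.8 = 35, which is 20%. I therefore show both rates. They correspond to 0.10 × 70 = 7 and 0.20 × 70 = 14 people without a primary value.

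**Bias with attenders only.** If attenders lose c on average, the true mean loss is (1 − d)c + d(c − D) = c − dD. Overstatement = dD.
- 10%: 0.10 × 5 = 0.5 kg
- 20%: 0.20 × 5 = 1.0 kg

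**Bias when a share r is retrieved.** The observed mean is c − D·dr/(1 − d(1 − r)), so the overstatement is D·[d − dr/(1 − d(1 − r))]. With r = 0.5:
- 10%: 5 × (0.10 − 0.05/0.95) = 0.50 − 0.263 = 0.24 kg
- 20%: 5 × (0.20 − 0.10/0.90) = 1.00 − 0.556 = 0.44 kg

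Range over r, same formula:

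| r | 10% missing | 20% missing |
|---|---|---|
| 0.25 | 5 × (0.10 − 0.025/0.925) = 0.36 kg | 5 × (0.20 − 0.05/0.85) = 0.71 kg |
| 0.50 | 0.24 kg | 0.44 kg |
| 0.75 | 5 × (0.10 − 0.075/0.975) = 0.12 kg | 5 × (0.20 − 0.15/0.95) = 0.21 kg |

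**Range over D, on the plan's own scale.** Suppose attenders achieve the planned loss and non-attenders keep 50% or 0% of it. Overstatement without retrieval:
- Meals: 13.6 × 0.10 × (0.5 to 1) = 0.68 to 1.36 kg at 10%; 1.36 to 2.72 kg at 20%.
- Produce: 6.8 × 0.10 × (0.5 to 1) = 0.34 to 0.68 kg at 10%; 0.68 to 1.36 kg at 20%.

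**Meals against produce.** With the same d and D in both arms the overstatement cancels. If D scales with the planned loss, the arm difference is overstated by 0.34 to 0.68 kg at 10% and 0.68 to 1.36 kg at 20%.

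**Power.** On the plan's ANOVA assumptions, 20% missing in the food arms (28 each) leaves omnibus power at 0.85 with 35 controls and 0.94 with 70.

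**The case against.** Several objections have force.

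**Stopping the food is not leaving the study.** A reader might infer that the endpoint is lost for everyone who stops. The documents do not support this: Table 1 schedules week 16 for all, without a condition on adherence. The point is confined to missed visits.

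**The text is silent, not prohibitive.** It does not forbid a chart weight at week 16, and a journal article may leave back-up sources to the full protocol. That stands as a limit. Still, the article does more than omit a detail: in two places it assigns a source to each time point and places the chart at six and 12 months.

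**The control source is inferred.** The sentence on the electronic record concerns how controls are identified. No passage states how, or in what window, their 16-week weight is taken. With retrospective review and no visit, the chart is the evident source, but that is an inference.

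**The sizes are modest and assumed.** At 10% missing and half retrieved, the fix removes 0.50 − 0.24 = 0.26 kg, which is 0.26/6.8 = 3.8% of the smaller planned difference. The documents give neither a deficit nor a retrieval rate.

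**One standardised source is a defensible choice.** Clinic weights are less standardised, are off the exact day and exist only for those who came to clinic. A weight at week 19 would fall about four weeks after the 15 weeks of food end, so it measures something a little different. This argues for a tight window and a sensitivity analysis, not for leaving the value missing.

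**Conclusion.** The point holds for food-arm participants who do not attend week 16. As written, they have no primary value, although their record will be reviewed later and may contain a weight near that date. If they lost less than attenders, the loss relative to controls is overstated: by 0.5 kg at 10% missing and 1.0 kg at 20% under an assumed 5 kg deficit, falling to about 0.24 and 0.44 kg if half are retrieved. These figures scale in proportion to the deficit and assume that the control mean is unaffected. Between the food arms the bias cancels wholly if missingness and deficit are equal, and otherwise in part when both arms are affected in the same direction.

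The protocol's remark on attrition might lead a reader to infer that the harm is lost power. The calculation does not bear this out for the omnibus test, which stays at about 0.85 or more with 20% missing. The harm is bias. This is a cheap improvement, not a flaw that undermines the design.

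**What to change.** In Demographic and clinical data, and as a note to Table 1:
- When the week-16 visit is missed and consent for chart use stands, extract the routine-care weight, HbA1c and blood pressure nearest week 16 within one pre-stated window.
- Set the same window for the controls' 16-week values, since none is stated now.
- Flag each value by source (study visit or chart).
- Repeat the primary analysis with study-visit weights only for the food arms.

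Fix the window before any outcome data are examined.

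The cost is a short additional chart review for about 7 to 14 people whose records are to be reviewed anyway. If half have a usable weight, 3 to 7 primary values are recovered. The downside is that these weights are less standardised and off the exact day, and some non-attenders will have none. The source flag and the visit-only analysis show how much the first two matter; the third leaves some bias in place.

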### Study design

This study is a parallel-arm quasi-randomized control trial with nonequivalent matched controls, which will be conducted between January 2022 and December 2023. Seventy adult patients recruited from our ambulatory practice will be randomly assigned to receive either: i) daily healthy frozen meals or ii) a weekly produce box and recipes for 15 weeks. Each study arm will comprise 35 patients with a documented diagnosis of obesity (body mass index [BMI] equal to or greater than 30kg/m^2^) and one or more of the following conditions: pre-type 2 diabetes/type 2 diabetes or hypertension. Participants will complete an in-person baseline visit and a follow-up visit at 16 weeks from baseline, and their medical charts will be reviewed for trends in these biomarkers at six months and 12 months from baseline. Healthy meals or a produce box will be shipped to the home address of participants once a week. Healthy meals provided in the study are low-sodium and diabetic-friendly ready-to-heat and serve breakfast, lunch, and dinner items. The produce box provided in the study will comprise fresh vegetables and fruits. For participants receiving a produce box, recipes utilizing items contained in the box will be available at the vendor’s website.

All participants will complete one individual medical nutrition therapy session via phone with a dietitian. The individual medical nutrition therapy appointment will occur within two weeks of enrollment in the study. A total of four nutrition and health videos, each under 10 minutes in length, will be available for participants to view between weeks 3 and 15 of the study. The complete study procedures are outlined in Table 1. Participants will be required to view the videos on healthy eating and weight loss and, as applicable to their health status, videos on type 2 diabetes and hypertension (see Table 2). The Healthie application (https://www.gethealthie.com/?afmc=a46i) will be utilized for nutrition education programming. Through the Healthie application, participants will receive automated text and/or email reminders to view educational videos. This feature is designed to drive compliance and completion of the nutrition education component. A report will be generated to provide completion percentage and other details based on participant engagement. The Healthie application is compliant with the US Health Insurance Portability and Accountability Act.

**Table 1. tbl1:** Schedule of study activities

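### Week-16 HbA1c is a study measurement in the food arms but depends on routine testing in the matched controls, so the three-group comparison can lose its matching on diagnosis

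*Protocol article*

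**What the plan says.** **Eligibility.** Under Study design, a participant needs obesity plus "one or more of the following conditions: pre-type 2 diabetes/type 2 diabetes or hypertension". Hypertension without any glycemic diagnosis is therefore enough.

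**HbA1c in the food arms.** Demographic and clinical data says "These data will be collected in-person at the baseline visit and at 16 weeks from baseline and via chart review of routine care at six"; the 12-month values likewise come from charts. Table 1 schedules HbA1c at both in-person visits with no restriction by diagnosis.

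**HbA1c in the controls.** The abstract says "Through retrospective chart review, patients who received standard of care will be matched to intervention group participants as controls". Study design adds that "Control group participants will be identified from the electronic medical record" once enrollment to the food arms is complete. Controls are "matched to intervention group participants based on BMI, diagnosis of pre-type 2 diabetes/type 2 diabetes, and/or hypertension". Having an HbA1c on file is not among the stated matching factors.

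**Analysis.** Study aims compares HbA1c with standard of care at 16 weeks, six months and 12 months, without limiting it to patients with pre-/type 2 diabetes, and labels this aim exploratory. Data analysis says "Separate repeated-measures ANOVAs will be conducted for each dependent variable with the between subjects factor group (healthy meals, produce box, and matched controls"), with two time levels: before the intervention and week 16. Missing data are to be handled by intention to treat, with no further detail. Strengths and limitations concedes missing chart data at six and 12 months. It does not mention control values at baseline or week 16.

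**The concern.** A repeated-measures ANOVA on two occasions needs two HbA1c values per person. A food-arm participant with hypertension only has both by protocol. The matched control has both only if a clinician happened to order them.

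If routine HbA1c is ordered less often in patients without a glycemic diagnosis, the controls who contribute will mostly have pre-/type 2 diabetes, while the food arms remain a mix. Matching on diagnosis is one of the few protections in this non-randomised contrast, and it would be lost for this outcome. HbA1c is likely to change differently in glycemic and non-glycemic patients. A difference between food and control could then appear, or be hidden, simply because of who could be measured.

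**Working it through.** The plan states no HbA1c figure to reproduce; its only sample-size calculation is for weight. The check therefore asks how far composition could shift over an assumed range.

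**Inputs from the article:** 70 controls; 35 participants per food arm; HbA1c scheduled for all food-arm participants at baseline and week 16.

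**Assumed inputs (not in the article):**
- h, the hypertension-only share: 10%, 20%, 30%, 50%
- (r, q), the chance that routine care recorded both HbA1c values in glycemic (r) and hypertension-only (q) controls: 90%/30%, 70%/10%, 50%/5%
- d, the background HbA1c change in glycemic patients of every group, with no food effect: -0.5 points; hypertension-only patients change by 0

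**Formulas:**
- Fraction of controls with both values: s = (1 - h)r + hq
- Glycemic share among those controls: g = (1 - h)r / s
- Spurious food-minus-control difference: d × [(1 - h) - g]

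**Worked case, h = 30%, rates 70%/10%:**
- s = 0.7 × 0.7 + 0.3 × 0.1 = 0.52, so 0.52 × 70 = 36.4 controls
- g = 0.49 / 0.52 = 94%, against 70% in the food arms
- difference = -0.5 × (0.70 - 0.942) = +0.12 points, against the food

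**Extremes of the range:**

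| h | r / q | Controls with both values (of 70) | Glycemic share, controls vs food arms | Spurious difference |
|---|---|---|---|---|
| 10% | 90% / 30% | 58.8 | 96% vs 90% | +0.03 |
| 30% | 70% / 10% | 36.4 | 94% vs 70% | +0.12 |
| 50% | 50% / 5% | 19.25 | 91% vs 50% | +0.20 (0.2045) |

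**Other assumed rates.** With h from 20% to 50% and rates of 100%/0%, 80%/10%, 60%/10% or 60%/30%, 24.5 to 56 controls have both values. Hypertension-only patients make up 0% to 33% of them, against 20% to 50% in the food arms.

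**Where the effect vanishes.**
- With equal rates, for example r = q = 70%, s = 0.70 and 49 controls remain, but g = 1 - h. Composition does not shift and the difference is zero.
- With d = 0 the difference is zero whatever the rates.
- The difference is proportional to d. A background rise of 0.5 points would give the same sizes in favour of the food.

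**Six and 12 months.** All groups then rely on charts. The same assumed rates would leave 35 × 0.275 = 9.6 to 35 × 0.84 = 29.4 participants per food arm. If rates are alike across groups, the loss is alike too: the values are fewer and selected, but the groups need not differ in composition.

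**The case against.** The strongest reply is that the bias needs a figure the article does not contain. Composition shifts only if hypertension-only patients are tested less often than glycemic patients, and neither rate is given. This stands. A reader might infer that most hypertension-only controls will certainly lack HbA1c; the documents do not support that.

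Second, controls are chosen retrospectively, so the full protocol may require usable chart values. That is possible, and the lack of look-back detail in an article is no fault. But the article does state its matching factors, and availability of HbA1c is not one of them.

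Third, nothing says that untested controls are dropped; missing data are to follow intention to treat. It is fair not to read deletion as stated. Yet intention to treat governs the group in which a person is analysed. It does not supply a value for someone never tested, and any imputation for hypertension-only controls would rest on the few who were tested.

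Fourth, a reader might extend the charge to six and 12 months. The documents do not support this as a between-group bias: every group relies on charts then, the stated ANOVA covers only baseline and week 16, and the limitations section already admits the missing data.

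Finally, the aim is exploratory, and with the assumed background fall the error runs against the food. Both points limit the stakes. The direction, however, depends on the sign of the assumed background change.

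**Conclusion.** The asymmetry at week 16 is fixed by the text: HbA1c is measured by protocol in all food-arm participants and only through routine care in controls, hypertension alone qualifies, and neither the matching nor the HbA1c analysis allows for this. Following the plan as written can therefore undo the matching on diagnosis for HbA1c at week 16.

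Whether it does, and by how much, rests on assumptions. Over the assumed range about 19 to 59 of 70 controls have both values, and a 0.5-point background fall confined to glycemic patients gives a spurious difference of about 0.03 to 0.20 points. With equal testing rates only numbers are lost.

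This concerns a secondary, exploratory outcome. The primary weight outcome and the randomised week-16 comparison of meals with produce are not affected. It is worth correcting because the correction is cheap.

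**What to change.** In Data analysis, replace the single three-group HbA1c ANOVA with the following:

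1. Compare meals with produce at week 16 from study-visit HbA1c in the randomised arms.
2. Limit the HbA1c contrast with standard of care to matched participants with pre-/type 2 diabetes, selecting controls who have HbA1c recorded in the same windows around baseline and week 16. Set the windows before controls are selected, and say how this rule sits with the intention-to-treat statement.
3. Report the number with HbA1c by group, diagnosis and time point.
4. Describe six- and 12-month HbA1c, in all groups, as applying to patients retested in routine care.

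This changes wording only; it adds no visit or test. The cost is a smaller HbA1c sample against controls, with conclusions limited to retested patients with glycemic disease. Some selection remains: the controls are those whose clinicians retested them, whereas food-arm participants are measured regardless. The report should say so.

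### Change in diabetes and blood pressure drugs is compared with matched controls although the drugs are recorded in person in the food arms and from charts in the controls, so ascertainment alone can create a difference in either direction

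*Protocol article*

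**What the plan says.** **Food arms.** The Demographic and clinical data section includes drugs among the data to be recorded: "hypertension diagnosis and classification, diabetes and blood pressure medications, and comorbid chronic conditions". It then fixes the source for the whole list: "These data will be collected in-person at the baseline visit and at 16 weeks from baseline and via chart review of routine care" (the latter for months six and 12). The Methods paragraph of the abstract says the same of the drugs by name: "diabetes and blood pressure medications will be collected in-person at the baseline visit and at 16 weeks from baseline".

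**Controls.** The abstract says: "Through retrospective chart review, patients who received standard of care will be matched to intervention group participants as controls". Study design says: "Control group participants will be identified from the electronic medical record", after enrolment of the intervention arms is complete. Strengths and limitations repeats it: "Study controls will consist of 70 matched participants identified via the electronic health record". No study visit for controls is described anywhere.

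**Analysis.** The secondary outcomes in Data analysis include "change in hbA1c, dosage, and number of diabetes medications; iii) change in dosage and number of blood pressure medications". Each dependent variable goes into a repeated-measures ANOVA with the "between subjects factor group (healthy meals, produce box, and matched controls") and two times, pre-intervention and week 16.

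**The concern.** The source of the drug data differs by group at exactly the two times that the ANOVA uses. A food-arm participant has a fixed contact at baseline and at week 16, when a change in treatment can be recorded. A control's chart records a change only if routine care entered it.

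Drug data also differ from weight or HbA1c in one respect. A control with no weight measured in the window has a visibly missing value. A medication list always returns an entry, so a control who was not seen can score a change of zero that looks like an observation. The plan's handling of missing data would not pick this up, and blinding the biostatistician does not remove a difference in source.

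At stake are four secondary outcomes (number and dosage, for two drug classes). They could be used to claim that food provision reduced the need for medication relative to standard of care. After week 16 the food arms move to chart review, so their own change from baseline to six or 12 months also mixes an in-person baseline with charted follow-up.

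**Working it through.** The protocol states no drug counts, stop rates, start rates or chart accuracy, so it has no figure of its own to reproduce here. The check is first a comparison of the sections, then an illustration.

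**1. Sources side by side**

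| Time | Meals | Produce | Matched controls |
|---|---|---|---|
| Baseline | in person | in person | chart |
| Week 16 | in person | in person | chart |
| 6 and 12 months | chart | chart | chart |

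Meals and produce share a source at every time. Each food arm differs from controls at both times in the ANOVA. Nothing in the text aligns them.

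**2. Direction**

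A recording error that is constant over time cancels in a change score. What matters is how completely changes during the 16 weeks are captured. Assume that every group has the same true probability *s* of stopping one drug and *t* of starting one. Assume also that food-arm capture is complete, and that control charts record a fraction *a* of stops and *b* of starts. Then

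expected change, food arms = −*s* + *t*

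expected change, controls = −*a·s* + *b·t*

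false difference (food minus control) = −*s*(1 − *a*) + *t*(1 − *b*)

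The first term favours the food arms and the second goes against them. The sign depends on four quantities, none of which the documents give.

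**3. Illustration**

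Every value of *s*, *t*, *a* and *b* below is an assumption. Rejection rates come from simulating 70 food-arm participants against 70 controls, with a two-sample t test on change at the 5% level and no true difference between groups.

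| *s* | *t* | *a* | *b* | False difference, drugs per patient | Rejection |
|---|---|---|---|---|---|
| 0.20 | 0 | 1 | – | 0 | about 5% |
| 0.20 | 0 | 0.75 | – | −0.20 × 0.25 = −0.05 | about 12% |
| 0.20 | 0 | 0.50 | – | −0.20 × 0.50 = −0.10 | about 38% |
| 0.20 | 0 | 0.25 | – | −0.20 × 0.75 = −0.15 | about 80% |
| 0.20 | 0.20 | 0.50 | 1 | −0.10 + 0 = −0.10 | about 19–20% |
| 0.20 | 0.20 | 0.50 | 0.50 | −0.10 + 0.10 = 0 | about 5% |
| 0.10 | 0.20 | 0.50 | 0.50 | −0.05 + 0.10 = +0.05 | about 10% |
| 0.10 | 0.20 | 0.25 | 0.25 | −0.075 + 0.15 = +0.075 | about 20% |

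In the last two rows nearly all rejections go against the food arms. With three groups of 35, 35 and 70, which is closer to the planned test, rows two to four give about 11%, 32% and 72%.

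The largest rates need three conditions together: nobody starts a drug, food-arm capture is complete, and charts miss most stops. Allowing starts that are fully charted roughly halves the 38%. Missing starts and stops alike, at equal true rates, removes the bias.

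**The case against.** **The in-person list may not be patient report.** This stands as a limit. The protocol describes these items as objective health data, groups them with diagnoses, and treats self-reported data separately when it discusses blinding. Visits take place at the patients' own practice, so the record may be consulted. If the in-person list is in fact taken from the record, one sentence saying so would settle most of the point. As written, though, the text separates in-person collection from chart review and assigns the drugs to the former at baseline and week 16.

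**Bias in favour of the food arms.** A reader might infer that equal true change must show as fewer drugs in the food arms. The documents do not support that. Charts could plausibly miss stops more than starts, since a start usually needs a prescription in the record. A stale list can also miss new or intensified treatment, and the bias then reverses.

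**A zero may be true.** For prescription drugs, no clinician contact often does mean no prescribed change. This is fair, and it is a reason not to set unreviewed control lists to missing. Doing so in controls alone would also select controls who are in clinical contact, which is a new bias.

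**Low stakes.** Drug number and dosage appear in none of the hypotheses under Study aims, and the protocol calls its secondary aim exploratory. It already discloses nonequivalent controls, the lack of a parallel control group and unblinded assessors. It does not disclose that the data source differs by group.

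**Conclusion.** The point holds as a lack of comparability. Followed as written, the plan compares in-person drug data with chart data on change from baseline to week 16, and a difference from controls can arise with no true effect. Neither its direction nor its size can be fixed from the documents. The illustrative range of −0.15 to +0.075 drug per patient, and the rejection rates with it, rest entirely on assumed stop, start and charting rates and on complete capture in the food arms. No single false-positive rate should be quoted as the error rate of this trial.

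Severity is low to moderate. Only secondary outcomes are touched. The primary weight outcome does not depend on drug data, and meals versus produce at week 16 uses the same source in both arms.

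**What to change.** 1. For every comparison with matched controls, take drug number and dosage from one source in all three groups: the electronic record's medication list at baseline (or the control's index date), week 16, six months and 12 months. This also removes the food arms' change of source after week 16.
2. Use the in-person list only for meals versus produce at week 16.
3. Apply one rule on list review to all groups. Report how many in each group had the list reviewed or updated by routine care in the window, and run a sensitivity analysis restricted to them. Do not set only controls' values to missing.
4. State as a limitation that study visits may themselves update the record, which can leave some difference in capture even with a common source.

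The cost is two extra chart reads per food-arm participant (2 × 70 = 140 in all) in records that the study already opens for six and 12 months. The comparison with controls also loses some detail relative to the in-person list.
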